### Statistical analysis plan

2.6.

All data quality monitoring and analysis will be overseen by the lead biostatistician. Distributions of baseline characteristics for participants will be compared between T-MD and usual care intervention groups to assess effectiveness of the randomization. Statistical or clinical differences will be adjusted for in secondary analyses. All analyses for treatment group comparisons will use an intention-to-treat approach and results will be reported using the CONSORT extension to non-pharmacological randomized trials. The primary outcomes for this study are NSI (Aims 1, 3), PGIC scores (Aim 1) and brain activation as measured by fNIRS (Aims 2, 3). The NSI and PGIC will be measured at baseline, 2 weeks, 4 weeks, and 3 months post randomization. Brain activation will be measured at baseline and 4 weeks. NSI and fNIRS will be treated as continuous and PGIC scores will be dichotomized into minimal or no change vs. moderate or greater change. For Aim 1, we will analyze the NSI score using linear mixed models with fixed effects for site, intervention, time, and the intervention by time interaction along with a random effect for subject to control for the correlation within person over time. We will use a generalized linear mixed model with a logit link and the same fixed and random effects for the dichotomized PGIC outcome. We will test each intervention’s effect over time using the intervention*time interaction. For Aim 2, we will calculate change scores by subtracting the fNIRS value at 4 weeks from the baseline value. We will use a two-sample t-test to compare the change scores between the intervention and control group. For Aim 3, we will calculate change scores by subtracting the NSI value at 4 weeks from the baseline value. The efficacy of the intervention will be determined based on the results for each outcome and interpreted within the domain of that specific outcome with no adjustment for multiplicity. Pearson correlation will be used to examine the relationship of change in NSI to the fMRI value at 4 weeks in the intervention group.

We also plan to explore factors (e.g., demographics, medical history, injury information, other symptoms, and impairments) that may influence the efficacy of T-MD on the outcomes of NSI, PGIC, and RTA. This will be done by focusing only on the 4-week time point and estimating within levels of each factor the intervention effect and 95% confidence intervals. We will also explore the independent effects of each treatment domain (e.g., anxiety/mood, cognitive, migraine, ocular, vestibular, sleep, autonomic) on primary and secondary clinical outcomes within the T-MD group using a mixed model with fixed effects for domain, time, and site along with a random effect for subject to control for the correlation within person over time. We will test each treatment domain’s effect over time using a domain*time interaction.

Calculations of sample size were based on the primary NSI primary outcome. We propose to randomize a total of 250 participants (125 in each intervention group) to allow approximately 200 participants for a complete case analysis at 4 weeks (assuming 20% attrition). With α = 0.05, two-tailed test, a sample size of 200 (*n* = 100 in each main effect group) will provide 80% power to detect a difference as small as 5 points on the NSI scale (standard deviation of 14) between the T-MD and usual care intervention groups assuming an autocorrelation of 0.7 for a 2 group repeated measures design with 4 repeated measures and AR (1) covariance structure. This sample size provides 99% power for the dichotomized PGIC (Aim 1) assuming 75% of the T-MD group and 50% of the control group reach moderate improvement and the same repeated measures design. Group sizes of 100 achieves 94% power to detect an effect size of 0.5 in fNIRS change using an independent samples, two-sided t-test (Aim 2, α = 0.05). For Aim 3, *n* = 100 in the intervention group provides 99% power to detect a Pearson correlation as small as 0.4. All power analyses were conducted in NCSS/PASS.

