### Allocation to study arms

2.2.

Participants will be screened and recruited from two concussion specialty clinics, and randomization will be stratified by site. Within site, a permuted block randomization with random block sizes with a 1:1 allocation ratio will be used. The lead biostatistician will generate the randomization list which will be uploaded into the electronic data capture system. The site coordinator will receive the allocation for each participant once all eligibility information is entered and the participant is deemed eligible for the trial. Participants will be randomized to either the T-MD or usual care intervention arm. Treating clinicians and study research staff will not be blinded to participant group, as they will be employing study procedures and supervising participants in the study. The Principal Investigators will be blinded to participant group assignment throughout the study, including during data analysis.

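### Covariates for the secondary adjusted analyses are to be chosen by observed baseline differences between arms, with no threshold, rather than named in advance for their relation to outcome

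*Protocol article*

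**What the plan says.** All of the analysis text is in section 2.6 (Statistical analysis plan) of the protocol article.

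- Baseline characteristics "will be compared between T-MD and usual care intervention groups to assess effectiveness of the randomization".
- The consequence follows at once: "Statistical or clinical differences will be adjusted for in secondary analyses". The section gives no test level, no size of difference that counts as clinical, and no list of covariates.
- The primary NSI analysis is fixed separately, as "linear mixed models with fixed effects for site, intervention, time, and the intervention by time interaction along with a random effect for subject", with the effect tested "using the intervention*time interaction". The dichotomized PGIC uses the same terms with a logit link.
- Baseline NSI enters as the first repeated measure: "The NSI and PGIC will be measured at baseline, 2 weeks, 4 weeks, and 3 months post randomization".
- For the fNIRS comparison in Aim 2: "We will use a two-sample t-test to compare the change scores between the intervention and control group".

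Section 2.2 (Allocation to study arms) says that, within site, "a permuted block randomization with random block sizes with a 1:1 allocation ratio will be used". The allocation is released only after eligibility has been entered.

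**The concern.** Two things are wrong with the rule as stated.

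First, its purpose is mistaken. If allocation follows section 2.2, differences between arms in characteristics fixed before allocation arise by chance. A significance test on them does not measure whether randomization worked.

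Second, the result of that comparison decides which covariates enter the adjusted analyses. A variable unrelated to outcome is as likely to be flagged as a strongly prognostic one, and a strongly prognostic variable that happens to balance is left out. The adjusted model depends on the observed data, and the clinical limb, having no threshold, leaves part of the choice to judgement after the arms have been compared.

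At stake is the value of the secondary adjusted analyses. They should show whether the conclusions survive adjustment for known prognostic factors, and with better precision where that is available. A set chosen by imbalance does neither reliably.

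**Working it through.** **Inputs from the article (section 2.6):** 5-point NSI difference, SD 14, 100 analysed per arm, two-sided 0.05, autocorrelation 0.7 with AR(1), four measures, stated power 80%.

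**Assumptions, because the article gives no figure:** a baseline test level of 0.05; a covariate–outcome correlation r of 0.3 to 0.7 (0.49 = 0.7², the AR(1) value two visits apart); clinical cut-offs of 0.1 or 0.2 standardized mean difference (SMD).

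**1. The plan's own power figure.** The standard error at a single time point is 14 × √(2/100) = 1.980. For the mean of four AR(1) measures the variance factor is [4 + 2(3×0.7 + 2×0.49 + 0.343)]/16 = 0.678, which gives 86.6% power. Compound symmetry at 0.7 gives a factor (1 + 3×0.7)/4 = 0.775 and 81.8%. The stated 80% is thus close to compound symmetry and not to AR(1) under this approximation. The difference is on the cautious side, and nothing below depends on it.

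**2. How often chance flags something.** Each covariate is flagged with probability 0.05 whatever its prognostic value (4.7–5.2% in simulation). For k independent covariates the chance of at least one flag is 1 − 0.95^k: 40% for k = 10, 64% for k = 20, 79% for k = 30. Table 2 lists 13 secondary instruments, and section 2.4.3 adds age, sex, mTBI history and migraine, so counts in this range are plausible. Correlated measures would lower the figures.

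**3. Share of the variance reduction kept.** Adjustment removes the part of the estimate due to chance imbalance. Adjusting only when |z| > c keeps the share 2[1 − Φ(c)] + 2cφ(c).

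- p<0.05, c = 1.96: 0.05 + 2×1.96×0.0584 = 0.279, so 28% is kept and 72% lost.
- SMD above 0.2, c = 0.2×√50 = 1.414: selected 16% of the time, 57% kept.
- SMD above 0.1, c = 0.707: selected 48% of the time, 92% kept.

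**4. Power at one 4-week comparison** (simulation, 10,000 runs per scenario, p<0.05 rule):

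| r | Unadjusted | Selected if p<0.05 | Pre-set covariate |
|---|---|---|---|
| 0.3 | 72.0% | 72.3% | 75.8% |
| 0.49 | 71.7% | 72.8% | 82.4% |
| 0.7 | 71.0% | 73.2% | 94.2% |

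The closed form agrees for the pre-set column: the standard error is 1.980 × √(1 − r²), giving 75.4%, 82.6% and 94.3%. At r = 0.49 the rule delivers (72.8 − 71.7)/(82.4 − 71.7) = 10% of the available power gain. With the clinical cut-offs at r = 0.49, power is 73.1% (SMD above 0.2) or 77.2% (SMD above 0.1), against 81.9% pre-set in the same runs.

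**5. Type I error.** Under the null, the p<0.05 rule rejects in 4.4% of trials at r = 0.49 and 3.8% at r = 0.7. It is slightly conservative.

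**6. The stated NSI mixed model.** With complete simulated data, adding a baseline covariate as a main effect left the 4-week interaction estimate and its standard error unchanged (for example −7.654, SE 1.603, both ways). With 20% dropout the standard error moved by less than 1%. What matters there is how baseline NSI is handled. For a 4-week comparison, the change score gives 70.6% power and conditioning on baseline gives 82.6% at r = 0.49; at r = 0.7 the figures are 90.3% and 94.3%.

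**7. Aim 2.** Conditioning on baseline fNIRS instead of testing change scores multiplies the variance by (1 + r)/2. The stated 94% power for an effect size of 0.5 becomes 98.4% at r = 0.49 and 97.0% at r = 0.7.

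**The case against.** The strongest reply is that this is a secondary matter in a condensed article. The primary models are fixed in advance, and a covariate list is commonly left to the statistical analysis plan. The first part stands. The second does not answer the point: the article does not leave the choice open, it states a rule, and a later list would have to override that rule.

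Four stronger readings are tempting, and the article does not support them.

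- *The rule gives up almost all of the available precision.* Even a p<0.05 rule keeps about 28% of the variance reduction, the clinical limb could keep far more, and the NSI interaction test has essentially nothing to gain from main-effect covariates. The power figures in step 4 describe a single-visit comparison and not that model.
- *The selection step raises the false-positive risk.* Step 5 shows the opposite.
- *The adjusted analyses are the only robustness check.* Section 3.3 (Limitations and future considerations) also plans a post-hoc evaluation of compliance, and the full plan is not shown.
- *Every baseline difference is chance by construction.* This is secure only for characteristics fixed before allocation. Section 2.5 schedules the baseline outcome assessment within 5–7 days of enrollment, and section 2.4.3 places the first fNIRS in the first week after enrollment. Neither puts these measurements before randomization, and treating and research staff are not blinded.

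**Conclusion.** The point holds for the secondary adjusted analyses only. The article fixes a data-dependent rule that selects on imbalance rather than prognosis, has no threshold, and rests on a mistaken purpose. It does not endanger the primary NSI and PGIC models or type I error.

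For a single 4-week comparison, the cost under an assumed p<0.05 rule is 72–73% power against 76–94% for r between 0.3 and 0.7. The true cost cannot be fixed from the article, because the clinical limb is undefined and could shrink the loss considerably. The benefit of pre-set covariates lies mainly with PGIC, return to activity, single-time-point analyses and, through baseline fNIRS, Aim 2. No figure was computed for PGIC or return to activity, so for those only the direction is argued. Low to moderate importance, but worth correcting because the correction is cheap.

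**What to change.** - Describe baseline characteristics by arm without significance tests, and drop the stated aim of judging the randomization by them.
- Replace the sentence on adjusting for observed differences with a fixed list of prognostic covariates for the secondary adjusted analyses, used whatever the observed balance. A suitable list is time since injury, age, sex, prior mTBI, migraine history and site, with baseline NSI added for PGIC and return to activity, and baseline fNIRS for the Aim 2 comparison.
- If an NSI analysis is to condition on baseline NSI, model only the post-baseline visits as the response, so that baseline NSI is not both response and covariate.
- Use only covariates measured before allocation. For baseline NSI and baseline fNIRS, first confirm that timing, since the article does not state it.

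Age, sex, mTBI history and migraine are named as collected in section 2.4.3, and time since injury is needed for eligibility, so no new data are required. The cost is a change of wording and minor extra analysis work, the largest part being the restructured response if the baseline-conditioned NSI analysis is added.

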#### Primary and secondary study outcomes

2.4.3.

Primary outcomes are the Neurobehavioral Symptom Inventory (NSI), Patient Global Impression of Change (PGIC), and Functional Near-infrared Spectroscopy (fNIRS). These primary outcomes represent different domains of function that are commonly affected following mTBI and provide different sources of information about the injury that inform clinical care decisions (i.e., treatment and/or rehabilitation). The NSI gathers specific information about mTBI symptoms. This measure is comprised of 22 items scored from 0 to 4 (0 total score represents no mTBI-related symptoms, 88 total score represents very severe levels of all 22 mTBI-related symptoms). The PGIC captures patient self-reported assessment of changes in their overall quality of life throughout their mTBI recovery. The prompt for the PGIC is: “Since beginning treatment at this facility, how would you describe the change (if any) in activity limitations, symptoms, emotions and overall quality of life related to your post-concussive condition?” The patient responds on a scale ranging from 0 (No change or condition has gotten worse), to 7 (A great deal better and a considerable improvement that has made all the difference). The fNIRS is a non-invasive imaging tool that measures changes in cerebral blood flow (CBF) and oxygenation in response to a behavioral task. The current study utilizes three neurocognitive tasks (WAIS symbol search and coding, and a flanker task) and a resting condition. Brain activation and deactivation in brain regions of interest (ROIs) will be examined and compared between groups within the first week following enrollment and at approximately four-weeks after enrollment. Secondary outcomes will include data from symptom, neurocognitive, balance, vestibular, sleep, and physical activity assessments (see Table 2). In addition, participant demographics and medical history data will be gathered as part of the normal clinical interview for mTBI (e.g., age, sex, history of mTBI, migraine). A daily text message-based assessment will be used to evaluate each participant’s compliance with their assigned intervention; and to assess frequency and intensity of at-home exercises in between the initial, 2-, and 4-week in-person study intervals. A FitBit Inspire 2 activity monitor will be provided to each participant to track activity and sleep throughout the 4-week intervention period. A detailed description of all study measures, scoring, and validity is presented in Supplemental material (see Description of Measures).

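### PGIC already measures change since treatment began, yet it is given a baseline value and tested by intervention-by-time; the stated 99% power belongs to a different test, the averaged group difference

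*Protocol article*

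**What the plan says.** Section 2.4.3 of the protocol article names PGIC as one of three primary outcomes and gives its prompt: "Since beginning treatment at this facility, how would you describe the change (if any) in activity limitations, symptoms, emotions and overall quality of life". The bottom of the scale, 0, means no change or worsening.

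Section 2.6 gives the schedule: "The NSI and PGIC will be measured at baseline, 2 weeks, 4 weeks, and 3 months post randomization". PGIC is then split into minimal or no change versus moderate or greater change. The model is borrowed from the NSI: "We will use a generalized linear mixed model with a logit link and the same fixed and random effects for the dichotomized PGIC outcome", that is, site, intervention, time, their interaction and a random subject effect. The next sentence names the test for both outcomes, each intervention's "effect over time using the intervention*time interaction". Efficacy is judged separately for each outcome, without multiplicity adjustment, so this test decides the PGIC result.

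The sample-size paragraph of the same section states: "This sample size provides 99% power for the dichotomized PGIC (Aim 1) assuming 75% of the T-MD group and 50% of the control group". It gives one pair of rates and no time course. The coding of time (categorical or linear) is not stated.

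**The concern.** For the NSI, baseline is a real pre-treatment level and intervention-by-time captures differential change from it. PGIC has no such level, because the patient's answer is itself the change. Its treatment effect is the between-arm difference at a visit after treatment has started. An interaction with time asks something else: whether that difference varies from visit to visit. A steady benefit on the logit scale gives no interaction among the post-baseline visits, however large the benefit is.

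Two things are at stake. An effective T-MD intervention could miss its primary PGIC test because its benefit is stable. And the reader is told that the test has 99% power when that figure describes another hypothesis.

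A secondary risk is that, with no responders at baseline in either arm, a logistic model with categorical time cannot estimate the baseline log-odds or the interaction terms referenced to it (separation).

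**Working it through.** **Inputs from section 2.6.** Two-sided α = 0.05; 100 analysed per arm; 75% versus 50% ("assuming 75% of the T-MD group and 50% of the control group reach moderate improvement and the same repeated measures design"); four measures; AR(1) correlation 0.7.

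**Step 1: reproduce the 99%.**

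*One visit.* Difference 0.25.
- Null SE (pooled) = √(2 × 0.625 × 0.375/100) = 0.0685.
- Alternative SE = √((0.1875 + 0.25)/100) = 0.0661.
- Power = Φ((0.25 − 1.96 × 0.0685)/0.0661) = 96.0%. With the unpooled SE throughout, Φ(0.25/0.0661 − 1.96) = 96.6%.

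*Average over four visits.* The variance is multiplied by the sum of the correlations divided by m²:
- [4 + 2(3 × 0.7 + 2 × 0.49 + 0.343)]/16 = 10.846/16 = 0.678.
- Unpooled power = Φ(0.25/√(0.004375 × 0.678) − 1.96) = 99.6%. Pooled 99.5%, logit scale 99.2%, compound symmetry 98.8%.

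*Average over the three post-baseline visits.*
- Factor [3 + 2(2 × 0.7 + 0.49)]/9 = 0.753.
- Power is 98.5% to 99.2% across the same variants.

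The stated 99% is therefore the power of a time-averaged group difference. The same paragraph also speaks of main-effect groups.

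**Step 2: what the interaction tests.** At visit t the arm effect is θ + γₜ, and the interaction test is γₜ = 0 for all t. A constant 75/50 gives a log odds ratio of ln[(0.75/0.25)/(0.50/0.50)] = ln 3 = 1.10 at every visit, so γ = 0 and power equals α.

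If equal, non-zero baseline rates are included, the interaction relative to baseline is the full 1.10, but imprecise. As a rough marginal guide:
- With 2% responders per arm, the baseline log odds ratio has SE √(2 × (1/2 + 1/98)) = 1.01.
- With 5%, it is √(2 × (1/5 + 1/95)) = 0.65.
- With 0%, it is undefined.

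**Step 3: simulate the planned test.** 100 per arm; 300 trials per scenario; binary data from thresholded AR(1) normals with correlation 0.7; random-intercept logistic model without the site term; 5% likelihood-ratio test of the interaction; visits at 0, 2, 4 and 13 weeks. Rates other than 75/50 are assumptions used to show the range. Simulation error is about 1 to 3 points.

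| T-MD/control % at 2 wk, 4 wk, 3 mo | Baseline, both arms | Categorical time | Categorical, baseline dropped | Linear time |
|---|---|---|---|---|
| 75/50 throughout | also 75/50 | 5% | 4% | 8% |
| 75/50, 75/50, 75/50 | 0% | 4% | 5% | 69% |
| 75/50, 75/50, 75/50 | 2% | 19% | 5% | 66% |
| 75/50, 75/50, 75/50 | 5% | 39% | 6% | 63% |
| 50/30, 75/50, 85/65 | 0% | 5% | 11% | 75% |
| 35/30, 75/50, 85/75 | 0% | 57% | 69% | 44% |
| 35/30, 75/50, 80/55 | 0% | 71% | 81% | 92% |
| 40/40, 75/50, 75/75 | 0% | 93% | 96% | 6% |

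No cell reaches 99%. With categorical time and four visits, a benefit of 20 to 25 points at every visit (fifth row) is found in 5% of trials. A benefit confined to 4 weeks (last row) is found in 93%.

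**The case against.** **The scenario is assumed.** The article gives one pair of rates and no trajectory. A difference that builds up to 75/50 by 4 weeks fits the wording just as well, and the interaction then has some power. This stands. A reader might infer that the interaction test has almost no power whatever happens, but the document does not support that. Near-α power needs a constant effect and categorical time, with baseline rates either empty or equal to the later ones.

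**Separation is not certain.** It requires categorical time, which is not stated, and no answer of moderate or greater change at baseline. Section 2.5 places the baseline assessment within 5–7 days of enrolment, after a first clinic visit, so a few positive answers are possible. This stands too. To say that the model is separated at baseline goes beyond the text; it may be. Separation would also leave contrasts among later visits estimable.

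**The 99% is not a miscalculation.** A reader might infer that it must be lowered. It is right for an averaged group difference and needs restating only if a single-visit contrast is chosen.

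**The SAP may settle it.** The coding of time could properly be left there. But the article itself fixes the baseline PGIC, the interaction as the test and the 99% claim, so the mismatch does not depend on anything unseen.

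**PGIC did not drive the sample size.** The NSI did. That lessens the consequences for design, but PGIC is still a primary outcome judged on its own test.

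**Conclusion.** The point holds in qualified form. Two parts do not depend on assumptions about trajectory or coding: a rating of change since treatment began has no informative baseline, and the named interaction is not the test whose power is quoted.

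The size of the loss does depend on them. With four visits, interaction power is:
- about 4–5% for a constant 75/50 with categorical time, when baseline is 0% or also 75/50 (19–39% with 2–5% baseline responders);
- about 63–69% with linear time and a near-zero baseline;
- about 5–93% with categorical time and rates that change over follow-up.

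None of the scenarios examined matches the stated 99%. These figures rest on 100 per arm, correlation 0.7, a model without site, and assumed trajectories. Separation at baseline is a possibility, not an established fault.

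**What to change.** 1. Remove baseline from the PGIC schedule and model; analyse 2 weeks, 4 weeks and 3 months.
2. Make the primary PGIC test one pre-specified 1-df between-arm contrast from that model. Either of two choices is sound: the contrast at 4 weeks, with power restated as about 96%, or the contrast averaged over the three post-baseline visits, with about 99% power, so that the stated figure can stand.
3. Report intervention-by-time for PGIC as descriptive only.
4. State in the power paragraph which contrast the figure refers to.

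The cost is a change of wording in the protocol and SAP and, if the 4-week contrast is chosen, a slightly lower stated power. No extra participants or visits are needed.

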**Methods:**

This study employs a single-blinded, two-group repeated measures design. The RCT will enroll up to 250 military-aged civilians (18-49 yrs) with a diagnosed complex mTBI within 8 days to 6 months of injury from two concussion specialty clinics. The two study arms are a T-MD intervention and a usual care, behavioral management control group. All participants will complete a comprehensive, multidomain clinical evaluation at their first clinical visit. Information gathered from this evaluation will be used to adjudicate mTBI clinical profiles. Participants will then be randomized to either the 4-week T-MD or control arm. The T-MD group will receive targeted interventions that correspond to the patient’s clinical profile (s) and the control group will receive behavioral management strategies. Primary outcomes for this study are changes from enrollment to post-intervention on the Neurobehavioral Symptom Inventory (NSI), Patient Global Impression of Change (PGIC), and functional near-infrared spectroscopy (fNIRS). Time to return to activity (RTA), and healthcare utilization costs will also be assessed.

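### The NSI model gives each arm its own baseline mean instead of adjusting for baseline NSI, which costs about 12 points of power at 4 weeks under the plan's own inputs

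*Protocol article*

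**What the plan says.** All references are to the protocol article.

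- **Visits (section 2.6).** "The NSI and PGIC will be measured at baseline, 2 weeks, 4 weeks, and 3 months post randomization".
- **Model (section 2.6).** The NSI is analysed with "linear mixed models with fixed effects for site, intervention, time, and the intervention by time interaction along with a random effect for subject".
- **Test (section 2.6).** "We will test each intervention’s effect over time using the intervention*time interaction".
- **Sample size (section 2.6).** "With α = 0.05, two-tailed test, a sample size of 200" (100 per group) "will provide 80% power to detect a difference as small as 5 points on the NSI scale (standard deviation of 14"), "assuming an autocorrelation of 0.7 for a 2 group repeated measures design with 4 repeated measures and AR (1) covariance structure". The listed visits come to four only if baseline is counted, so baseline NSI is an outcome in the model.
- **Adjustment (section 2.6).** Baseline characteristics are compared between arms, and "Statistical or clinical differences will be adjusted for in secondary analyses". Baseline NSI is not a covariate in the primary model, and the arms are not constrained to share a baseline mean.
- **Outcome definition (Abstract, Methods).** "Primary outcomes for this study are changes from enrollment to post-intervention on the Neurobehavioral Symptom Inventory (NSI") and the other two primary measures. The intervention lasts 4 weeks, and the sample size provides for about 200 complete cases at 4 weeks.

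**The concern.** A free intervention main effect, with baseline as the first outcome, asks the model to estimate a baseline difference between arms. If baseline NSI precedes allocation, randomization makes that difference zero in expectation. Estimating it adds noise to every interaction contrast.

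With time as a factor and complete data, the interaction contrast at a visit is exactly the between-arm difference in mean raw change, whatever covariance structure is fitted. An observed baseline difference is then subtracted in full. Adjustment would subtract only the fraction ρ of it, which is the part expected to persist.

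At stake is precision in the main clinical comparison: a real 5-point benefit is more likely to be missed, and the confidence interval is wider than the data allow. The point concerns how baseline NSI enters the mean model. It is separate from the choice of covariance structure and from which visit or contrast is tested.

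**Working it through.** **Inputs, all from section 2.6.** Difference 5 points; SD σ = 14; n = 100 per arm; two-sided α = 0.05; AR(1) with 0.7 between adjacent visits; four visits including baseline. The correlations with baseline are therefore 0.7 at 2 weeks, 0.7² = 0.49 at 4 weeks and 0.7³ = 0.343 at 3 months.

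**1. The plan's own 80%.** Take the 3-df intervention-by-time test with baseline as one of four outcomes, and assume arm differences of 0, 5, 5, 5 (the article does not give the profile). The noncentrality is 11.06. Power is 80.6% by chi-square, or 79.8% to 80.3% by noncentral F (denominator df 196 to 594). The stated 80% is reproduced, which supports this reading of the model. A difference averaged over all four visits would give 86.6%, which does not match.

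**2. Equivalence with the raw change score.** A random-intercept model with site, arm, categorical time and arm by time was fitted to one simulated complete data set. The 4-week interaction coefficient was −3.9334, and so was the raw difference in mean change.

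**3. The 4-week contrast (ρ = 0.49), noncentral t.**

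- As written: SD of change = 14 × √(2 × 0.51) = 14.14; SE = 14.14 × √(2/100) = 2.00; power 70.1%.
- Baseline-adjusted: SD = 14 × √(1 − 0.49²) = 12.20; SE = 12.20 × √(2/100) = 1.73; power 82.2%.
- Variance ratio: (1 + 0.49)/2 = 0.745.
- Completers per arm for 80% power: 127 as written, 95 adjusted.
- A plain 4-week comparison that ignores baseline (SD 14) has 71.0% power, so the written contrast gains nothing from baseline at this visit.

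In 20,000 simulated trials, power was 70.2% and 82.0%.

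**4. Other visits and correlations, 5-point difference.**

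| Correlation with baseline | As written | Adjusted |
|---|---|---|
| 0.70 (2 weeks) | 90% | 94% |
| 0.49 (4 weeks) | 70% | 82% |
| 0.343 (3 months) | 59% | 76% |
| 0.30 (assumed, for range) | 57% | 75% |

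**5. The test the plan names (3 df, all visits, AR(1) 0.7, chi-square).** The comparison is with the joint test of the three post-baseline differences under one shared baseline mean. The profiles are assumptions.

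| Arm difference at the four visits | As written | Shared baseline mean |
|---|---|---|
| 0, 5, 5, 5 | 81% | 91% |
| 0, 2.5, 5, 5 | 55% | 74% |
| 0, 1.67, 3.33, 5 | 43% | 61% |
| 0, 2.5, 5, 2.5 | 63% | 71% |
| 0, 5, 2.5, 0 | 90% | 91% |
| 0, 0, 5, 0 | 96.4% | 96.5% |

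With a constant correlation of 0.7 and profile 0, 5, 5, 5, power is 93.3% against 97.8%.

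**6. Chance imbalance.** The SE of the baseline difference is 14 × √(2/100) = 1.98 points. An imbalance of that size is expected to carry 0.49 × 1.98 = 0.97 points into week 4, but the change score subtracts all 1.98. The 4-week estimate moves by 1.01 points, which is about a fifth of the 5-point target. Adjustment removes this shift on average.

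**The case against.** The strongest reply is that nothing here is invalid. A mixed model with baseline as an outcome is conventional, and under randomization it estimates the mean difference without bias. The sample size appears to have been computed for this model and reaches its target. That stands: the finding is lost efficiency, and the stated 80% is not wrong.

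Second, the 12 points belong to a 4-week contrast, whereas the plan tests the interaction over all visits. This is a fair limit on the headline figure. The named test also loses power, but the loss runs from almost nothing for a fading or isolated effect to 18 points for a growing one. Week 4 still matters, because it is the end of the intervention and the visit for which completers are counted.

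Third, the size depends on the correlation. A random subject effect alone implies constant correlation, and at 0.7 throughout the 4-week loss is 4 points. This stands as a range; the direction does not change for any ρ below 1.

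Fourth, equal true baseline means require baseline NSI to precede allocation. Sections 2.2, 2.5 and 3.2 do not make the order fully clear: baseline is scheduled several days after enrollment, and a message about the assigned intervention goes out the day after enrollment. This bears on the choice of fix. A shared baseline mean assumes the order, while baseline as a covariate does not impose that constraint. A baseline taken after allocation would also compromise the change score.

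Fifth, the article adjusts for observed imbalances in secondary analyses. This does not restore precision to the primary analysis, and adjustment chosen after seeing the imbalance is weaker than adjustment fixed in advance. Defining the outcome as change is no obstacle either: with baseline as a covariate, analysing change or the follow-up score gives the same treatment effect.

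**Conclusion.** The concern holds. The primary NSI model leaves unused precision that the trial already collects. Under the plan's inputs, power for 5 points at 4 weeks is 70% as written and 82% with baseline adjustment. For the interaction test over all visits with a constant effect it is 81% against 91%.

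These figures assume 100 completers per arm, 0.7 as the adjacent-visit correlation under AR(1), time as a factor and complete data; the article does not state how time is coded. The 4-week gain runs from 18 points at a baseline-to-week-4 correlation of 0.3 to 4 points at 0.7. On the overall test it can be 1 point or less. No scenario examined favours the written model. This is a change that should be made for efficiency; it does not correct a bias.

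**What to change.** In section 2.6, replace the NSI model sentence with one of these:

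- **(a) Shared baseline mean.** Keep all four visits as outcomes, with fixed effects for site, time and intervention by post-baseline visit, and no intervention main effect. Participants with only a baseline value stay in the model. Use this only if baseline NSI is confirmed to precede allocation.
- **(b) Baseline as covariate.** Take NSI at 2 weeks, 4 weeks and 3 months as outcomes, with fixed effects for site, intervention, time, intervention by time, baseline NSI and baseline NSI by time.

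In either case, state that the test is of the baseline-adjusted arm difference, at a named visit or jointly over the three post-baseline visits. Under (b) the intervention-by-time term alone would no longer serve, because it would test only whether the effect varies between post-baseline visits.

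The cost is one sentence of plan wording and a small change in model code. No extra participants, visits or data are needed. Make the change before any unblinded analysis.
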